## Data analysis

### Quantitative analysis

Quantitative data obtained through patient questionnaires will be analysed using GenStat statistical system (Release 14.2) and verified using Statistical Package for the Social Science (SPSS V22). Statistical significance will be claimed at *p* <0.05. Descriptive statistics will be used to characterise the study population, and any baseline differences between patients in the control and intervention groups.

The primary endpoint of pain intensity will be compared between groups to determine differences between the intervention and control (usual care). A linear mixed model analysis will be used to calculate the F-test to compare the means of the groups. In a supportive analysis, the REML method will be used to estimate, and if necessary adjust for, period effects. Other outcome measures such as preference for participation, control preference and perceived participation in care will be used to make comparisons between groups and the analyses will use a linear mixed model approach and analogous methods developed for binary and categorical data.

### Qualitative analysis

Qualitative data obtained through questionnaires and patient interviews. Patient participant interviews will be tape recorded and transcribed in full. A critical step in this study relates to evaluating the intervention, i.e. whether the multimedia intervention changed the way patients interacted with clinicians in order to achieve their goals of recovery. This is a fundamental aspect of the process evaluation. The interview transcripts will be analysed using quantitative content analysis [46]. A structured, systematic coding scheme will be applied to the textual data in order to compare intervention and usual care content for each of the four goals of recovery addressing the five main concepts of:Knowledge of the goal;Engagement with achieving the goal;Attitudes towards participation;Perceived barriers to participation;Perceived enablers to participation.

The unit of analysis will be text in the transcripts that refers to one of the four goals of recovery to be analysed. Several steps will be taken to conduct these analyses:The team will review 14 randomly selected transcripts (7 intervention and 7 non-intervention transcripts) to determine if the narrative could be relied on to provide sufficient information to conduct the analyses intended and identify coding rules for the five goals of recovery in the multimedia intervention.Coding rules will be developed in this process.These coding rules will be applied independently by all the investigators to assess the usability, ease and inclusiveness of the coding rules, and pilot test the inter-rater reliability of the coding rules on another randomly selected 10 transcripts.Once there is agreement about the coding process, a coding book will be developed and the remaining transcripts will be coded.The coding will be done by the researcher and an independent coderOnce coding is completed, the research team will conduct inter-rater reliability measures including percentage agreement. Inter-rater agreement greater than 80 % is considered acceptable [47]Minor discrepancies between the coders will be resolved by examining the data together.Major discrepancies will be resolved by independent review by two other members of the research team.

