### Multimedia goals of care intervention

The multimedia program was developed specifically for TKR patients by Enlighten Health®, a medical multimedia production company specialising in validated content for patient and clinical education. The multimedia intervention is presented in a format that combines text, sound, graphics and animation to provide information to patients in relation to postoperative recovery and goals of care for each day, up to 5 days following a TKR.

The multimedia program intervention, is designed to be both nurse-led, where the nurse assists the patient to navigate through the program, and patient self-directed; it is delivered to patients as a stand-alone program package on an iPad™. The intervention is designed with tailored information about the expected postoperative recovery on each day from Day one (1) to Day five (5) (or day of discharge) after TKR surgery. Embedded throughout the program is the importance of adequate pain management in order to achieve daily goals of recovery. The aim of the intervention is to facilitate an interaction between patients and their nurse each postoperative day about the specific goals and plans of care for each day of recovery after TKR surgery. The three main goals of recovery for patients after TKR surgery are: 1) to manage pain, 2) promote mobility of the knee joint to improve function and 3) avoid complications such as thromboembolism [16].

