#### Intervention application procedure

Daily, until discharge from the ward, following nursing handover and after patients’ morning meal (approximately 0900 h), the nurse allocated to care for a patient enrolled in the study reminds the patient to view the corresponding day’s goals of care package on the iPad™. The iPad™ is secured to the patient’s bedside to allow easy access to the program any time of the day or night and in addition, patients’ relatives can also view the presentation. It is anticipated that after viewing the goals of care animation, patients together with the nurse will discuss the patient’s goals for the day.

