#### Day 3 – data collection

Data will be collected from each participating patient in a cohort of a ward (A or B conditions) on postoperative Day 3. On this day, patients will be interviewed by the researchers and invited to respond to questions about their pain intensity, interference of pain on activities of daily living and to describe processes of care and interactions with clinicians relating to their goals of recovery. In addition, patients on the intervention ward (B) will also be invited to respond to questions related to the intervention. Table 2 outlines the concepts, measures and tools used during this data collection period.

**Table 2 Tab2:** Concepts measured and tools used for primary and secondary outcomes

Concept measured on day 3	Tool used
1. Pain intensity	• Numerical Rating Scale (NRS) [31]
2. Pain quality	• American pain society outcome questionnaire (APSOQ) (Cronbach α = 0.85) [32]
3. Pain treatment and management	• Medial record audit
4. Preference for participation	• Patient Activation Measure (PAM) • Control Preference Scale (CPS)

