### Process evaluation

The process evaluation is designed to examine the delivery of the intervention and understand the effects (or not) in the context of acute care delivery [38]. In order to know if the multimedia intervention was successful or not, in reducing patient participant pain intensity scores on Day 3, underlying processes need to be examined.

Process evaluation in this trial will include patient participant semi structured interviews on Day 3 post operatively of all participants, to examine patient barriers and facilitators to participation in care. Specific questions will be asked of participants relating to their goals of recovery in order to describe processes of care and interactions with clinicians. In addition to the interviews, field notes will also be kept by the researches to record information about ward culture and organisational environment that may impact on patients’ ability to participate.

Medication chart and medical records audits will be conducted on Day 3 to elicit information regarding prescribing and administration of analgesia. Furthermore medical records will be audited for documentation regarding pain though out the 24 h period on Day 3, this will give us details of the management and recording of patient participants’ pain.

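### Interview content is compared between arms on any text about a recovery goal, but only intervention patients are asked extra questions about the goals-of-care programme

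*Protocol article*

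**What the plan says.** Under Process evaluation, the protocol article plans "patient participant semi structured interviews on Day 3 post operatively of all participants". The shared content is described there: "Specific questions will be asked of participants relating to their goals of recovery in order to describe processes of care and interactions with clinicians".

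The section Day 3 – data collection adds a set of questions for one arm: "In addition, patients on the intervention ward (B) will also be invited to respond to questions related to the intervention". The intervention is a multimedia programme built to "provide information to patients in relation to postoperative recovery and goals of care for each day" (Multimedia goals of care intervention). Each morning the nurse "reminds the patient to view the corresponding day’s goals of care package on the iPad™" (Intervention application procedure).

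Under Qualitative analysis: "Patient participant interviews will be tape recorded and transcribed in full". A coding scheme is then applied "in order to compare intervention and usual care content for each of the four goals of recovery", under five concepts: knowledge, engagement, attitudes, barriers and enablers. The eligible text is defined as follows: "The unit of analysis will be text in the transcripts that refers to one of the four goals of recovery to be analysed". The coding rules are to be developed from 14 transcripts, seven per condition, piloted on 10 more, and then fixed in a coding book.

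**The concern.** A comparison of what patients say is fair only if both groups had the same opportunity to say it. Here the eligible text is defined by its subject (a goal of recovery) and not by the question that prompted it. The additional questions go to one arm and concern a programme whose subject is the goals being coded. Any goal statement given in reply is eligible under the stated rule, and control transcripts have no matching section.

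The article calls this evaluation step critical and fundamental to the process evaluation, which is meant to explain why the intervention did or did not work. If the pain result were null, a difference in coded knowledge or engagement could be read as evidence that the intervention changed participation, when part or all of it came from the longer interview.

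**Working it through.** **Setting the sections side by side**

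1. All participants in both arms are interviewed on Day 3 and asked about their goals (Process evaluation).
2. Intervention-ward patients alone are asked further questions (Day 3 – data collection).
3. Those questions concern a goals-of-care package (Multimedia goals of care intervention; Intervention application procedure).
4. Interviews are transcribed whole, any text on a goal is eligible, and the coded content is compared between arms (Qualitative analysis).
5. No section confines the comparison to the common questions, sets the intervention-only answers aside, or allows for the longer interview.

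Steps 1 to 4 give unequal opportunity for codable text. Nothing stated in the article removes it.

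**Number of transcripts**

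The article's total is reproduced: 2 wards × 4 periods × 30 patients = 240 (Sample size calculation). Each crossover ward has two intervention and two control cohorts, so each condition has 2 × 2 × 30 = 120 patients. Controls on the overflow ward are left out.

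**Illustration 1: share of patients with a codable statement on a goal, no true effect**

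Let p be the share who make such a statement in reply to the common questions, equal in both arms. Let q be the share of the remainder who make one only in reply to the extra questions. Both are assumptions; the article gives neither.

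- Control share = p
- Intervention share = p + (1 − p)q
- Spurious gap = (1 − p)q
- z = gap / √(2 × p̄(1 − p̄)/120), where p̄ is the mean of the two shares

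| p | q | Intervention share | Gap (points) | z |
|---|---|---|---|---|
| 0.30 | 0.20 | 0.44 | 14 | 2.25 |
| 0.30 | 0.30 | 0.51 | 21 | 3.31 |
| 0.50 | 0.20 | 0.60 | 10 | 1.56 |
| 0.50 | 0.30 | 0.65 | 15 | 2.35 |
| 0.80 | 0.20 | 0.84 | 4 | 0.8 |
| 0.80 | 0.30 | 0.86 | 6 | 1.2 |
| 0.95 | 0.20 | 0.96 | 1 | 0.4 |
| 0.95 | 0.30 | 0.965 | 1.5 | 0.6 |

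The z column only sets the gap against sampling error. It ignores clustering, and the article states no significance test for coded content.

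**Illustration 2: amount of coded text, no true effect**

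Assume k common questions and m extra ones, each with the same chance p of yielding codable goal text in either arm. Expected counts are then in the ratio (k + m)/k. With k = 4 or 8 and m = 1, 2 or 4, the ratio runs from 9/8 ≈ 1.12 to 8/4 = 2.00. The share with any goal text is 1 − (1 − p)^k against 1 − (1 − p)^(k+m). At p = 0.1 this gives 0.344 against 0.410 (k = 4, m = 1) and 0.570 against 0.651 (k = 8, m = 2).

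**After the fix**

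If only answers to the common questions are compared, m = 0. The expected ratio is then 1.00 and the spurious gap is zero in both illustrations.

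**The case against.** The strongest reply is that the interview guide is not shown. The extra questions might be few, closed (how often the programme was viewed, how easy it was to use), or not part of the recorded narrative. In addition, every patient in both arms is asked directly about goals, so the common questions may already draw a statement from most patients, and the gap is then a few points at most. Both arguments stand. They limit the size that can be claimed, but they do not change the stated rule, which admits the extra answers whenever they touch on a goal.

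A second reply is that the coding rules are still to be written, and a journal article may leave them to a fuller document. That would answer a complaint about missing detail. Here, though, the article fixes both the eligible text and the arm-specific questions, and these two statements conflict with a fair comparison. The coding book could repair this, but nothing in the article says that it will. The 80% agreement threshold and the second coder do not help: two coders can agree fully on text that only one arm was prompted to give.

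Three stronger readings may tempt a reader, and the document supports none of them:

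- **Intervention patients are bound to show more knowledge and engagement even if the programme does nothing.** The replies could equally add coded barriers or negative attitudes, and there may be few of them.
- **The coding is biased because coders can recognise the condition.** The article is silent on masking and does not say that the coding researcher is the interviewer. That is a separate matter of detail which an article may omit.
- **The trial's effectiveness result is compromised.** The primary endpoint is a 0–10 pain rating, and the listed secondary outcomes are not derived from coded transcripts.

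**Conclusion.** The point holds, within the process evaluation only. As written, the between-arm comparison of interview content gives the intervention arm more opportunity to produce codable goal text, so the arms can differ on the five concepts with no true effect.

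The size cannot be derived from the document. Under the assumed rates in illustration 1, the spurious gap runs from about 1 point, where nearly all patients already mention a goal in reply to the common questions, to 21 points, where only 30% do. Both illustrations assume that the extra questions yield some codable goal text and that each mention counts. If concepts were scored only from the common answers, the problem would disappear. No false-positive rate can be attached to it, since no test on coded content is planned.

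**What to change.** In Qualitative analysis and in the coding book, state that the between-arm comparison uses only text given in answer to questions put to both arms. State also that answers to the intervention-only questions are coded separately and reported as implementation data for the intervention arm.

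The cost is one or two sentences and some segmentation of the intervention transcripts. Goal statements made only in the intervention-only block leave the arm comparison but are still reported. The change does not depend on altering the interviews, which matters because Trial status places the trial in its last phase of data collection; moving the extra questions to the end would now reach few patients. Mentions of the programme in the common section should stay in, because removing them could delete genuine evidence on enablers and engagement.

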## Trial status

Trial status at the time of manuscript submission is ongoing. The trial is currently in the last phase of data collection.

## Discussion

The purpose of this research program is to develop, implement and evaluate a nurse-led multimedia, education intervention to improve postoperative outcomes for patients having TKR surgery. Our previous work in relation to patient participation in acute care has shown very low levels of patient involvement in care. In order to understand the complexities of facilitating patient participation in recovery after surgery, interventions to improve the capability of patients to participate need to be developed and evaluated. Evidence of the effectiveness of interventions that influence patient participation, on patient outcomes in the acute postoperative context, is not available. The outcomes of this research will inform the vital aspects of patient involvement in care processes and importantly provide evidence for the effectiveness of participation in improving patient outcomes after surgery.

## Abbreviations

APSOQ-R, American pain society’s patient outcome questionnaire; CPS, control preference scale; NRS, numerical rating scale; OKS, Oxford knee score; PAM, patient activation measure; TKR, total knee replacement
